## Abstract

**Background:**

Effective approaches that engage men in weight loss and lifestyle change are important because of worldwide increases, including in Canada, in obesity and chronic diseases. Football Fans in Training (FFIT), developed in Scotland, successfully tackled these problems by engaging overweight/obese male football fans in sustained weight loss and positive health behaviours, through program deliveries at professional football stadia.

**Methods:**

Aims: 1) Adapt FFIT to hockey within the Canadian context and integrate with Health*e*Steps™ (evidence-based lifestyle program) to develop Hockey Fans in Training (Hockey FIT); 2) Explore potential for Hockey FIT to help overweight/obese men lose weight and improve other outcomes by 12 weeks, and retain these improvements to 12 months; 3) Evaluate feasibility of recruiting and retaining overweight/obese men; 4) Evaluate acceptability of Hockey FIT; and 5) Conduct program optimization via a process evaluation. We conducted a two-arm pilot pragmatic randomized controlled trial (pRCT) whereby 80 overweight/obese male hockey fans (35–65 years; body-mass index ≥28 kg/m^2^) were recruited through their connection to two junior A hockey teams (London and Sarnia, ON) and randomized to Intervention (Hockey FIT) or Comparator (Wait-List Control). Hockey FIT includes a 12-week Active Phase (classroom instruction and exercise sessions delivered weekly by trained coaches) and a 40-week Maintenance Phase. Data collected at baseline and 12 weeks (both groups), and 12 months (Intervention only), will inform evaluation of the potential of Hockey FIT to help men lose weight and improve other health outcomes. Feasibility and acceptability will be assessed using data from self-reports at screening and baseline, program fidelity (program observations and coach reflections), participant focus group discussions, coach interviews, as well as program questionnaires and interviews with participants. This information will be analyzed to inform program optimization.

**Discussion:**

Hockey FIT is a gender-sensitive program designed to engage overweight/obese male hockey fans to improve physical activity and healthy eating choices, thereby leading to weight loss and other positive changes in health outcomes. We expect this study to provide evidence for a full-scale confirmatory pRCT.

**Trial registration:**

NCT02396524 (Clinicaltrials.gov). Date of registration: Feb 26, 2015.

## Background

A significant proportion of men of all ages are overweight or obese. In 2014, 21.8 % of Canadian men self-reported height and weight that classified them as obese (i.e., using body mass index, BMI) and 40.0 % of Canadian men were classified as overweight [1]. A recent study by the Global BMI Mortality Collaboration, analyzing records of 3.95 million people from 189 studies worldwide, showed that men had higher all-cause mortality for every additional five BMI points over 25 kg/m^2^ (relative to BMI 20–25 kg/m^2^), compared to women (hazard ratios and 95 % CIs: 1.51 (1.46–1.56) for men vs 1.30 (1.6–1.33) for women) [2]. The increased risk of death was also higher in younger people [2].

Men suffer poorer health outcomes on many measures of health status compared to women [3–5]. Men seem less knowledgeable about health risk factors [6]; and are less likely to access, interpret and apply information to maintain and improve their health [7]. According to the 2012–2013 Canadian Health Measures Survey, only 24 % of men achieved the recommended levels of physical activity, and the majority spent their waking hours being sedentary [8]. Despite this, the issue of gender is often neglected when planning and implementing health promotion and chronic disease prevention and management strategies.

Chronic diseases share several lifestyle risk factors including obesity/overweight status, physical inactivity, sedentary lifestyle, unhealthy eating habits and low health literacy, which if reduced, could prevent or eliminate most chronic diseases and their complications [9]. In Canada, these trends [1], which are more pronounced in rural and small urban settings, may help explain the higher prevalence of type 2 diabetes mellitus and increased mortality rates found in these regions [10]. Since 2003, there has been a steady increase in the number of men who are obese in Canada; in 2003, 16 % of men were obese compared to 21.8 % in 2014 [1]. These trends are alarming and pose threats to men’s individual health and the health care system as a whole.

Men may deny illness or delay treatment, ignore health concerns or engage in high-risk behaviours to prove adherence to the construct of masculine toughness or strength [3, 11–14]. Men’s behavioural choices are also influenced by culture, class, ethnicity, context, age and life events [3]. Even so, increasing evidence shows that when gender issues are used to inform program design and delivery, men will engage in weight management initiatives [12, 15–17]. Men may also be more open to participating in physical activity that is linked in some way to sport, athleticism, and competition [18] Although this could exclude certain settings or ages, there is evidence that walking – a universally accessible form of physical activity – is appealing, at least when introduced within the right context [19].

While health promotion programs targeting men have been implemented in other countries including Australia and the United Kingdom [20], programs have only recently started to emerge in Canada [21], and few options exist, particularly in rural and small urban regions of Canada where the burden of chronic disease is greater [10]. In general, men are reluctant to engage in healthy lifestyle and weight loss programs, seem less aware than women of their overweight status [22, 23], and associate increased body size with muscularity and masculinity [24, 25].

Physicians can play an important role in the dissemination of physical activity recommendations [26], as approximately 82 % of Canadians have reported having a regular doctor place they go for care [27], Most physicians, however, do not regularly assess or prescribe physical activity as part of a routine care, and even when discussed, few provide specific recommendations [28].

In a survey conducted in men living in small urban and rural communities in Canada, we found the following healthy lifestyle strategies appealed to men: 1) physical activity goals set with the help of a coach; 2) training for an event such a charity walk or sport; 3) in-person sessions with a coach and their peers in a fun atmosphere; and 4) technology-supported healthy lifestyle tools. A common theme that arose from our survey was the importance of support from other men. Men also frequently indicated that they would be motivated to lead a healthier lifestyle if it made them feel better (e.g., more energy, less pain, better sleep) and improved their fitness and memory [29, 30].

Men appear to harbour misperceptions about the dietary behaviours required to lose weight [23, 31, 32] and perceive dieting and organized weight loss programs as ‘feminized’ domains [33]. Hence, interventions that target men will be more likely to succeed if they encompass physical activity as well as diet [34, 35] and similar to our findings, if they include peer groups they can identify with [12, 16, 36]. Programs situated in a sporting context where participants had a strong sense of affiliation have been found to be both effective and to have low dropout rates, due to high ratings of participant satisfaction [7, 17].

The social and psychological connections (e.g., identity, validation, belonging) that being a fan creates are powerful [37], and this is particularly true in group contexts [36]. Using a pragmatic Randomized Controlled Trial (pRCT) design, Football Fans in Training (FFIT), a gender-sensitised, weight loss and healthy living program developed for delivery to men through Scottish professional football clubs by club coaches [15], demonstrated that the professional football club setting was a powerful ‘draw’ for overweight and obese men at high risk of future ill-health across the socio-economic spectrum and clinically significant weight loss and cost-effectiveness 12 months after baseline measures [38].

Canadian hockey is core to Canadian culture: two-thirds of adult Canadians follow the game as a fan and 8 out of 10 identify hockey as a key part of what it means to be Canadian [39]. In many areas, particularly small towns and rural areas, junior hockey clubs are the primary fan-base. These junior hockey clubs are often a rallying point in these communities, attracting a large number of fans (disproportionately male) to games, often more than in urban areas. The Ontario Hockey League (OHL), a semi-professional Junior A hockey league, is a member of the Canadian Hockey League, with one of the world’s largest hockey fan-bases; for example, last season, more than 9 million fans attended Canadian Hockey League games, many in small urban centres [40].

Hockey Fans in Training (Hockey FIT) may provide a preferred sport-fan venue to engage at-risk Canadian men. Hockey FIT will be based on FFIT, but adapted to hockey within the Canadian context, and, to strengthen sustainability, will be integrated with components of our lifestyle prescription program (Health*e*Steps™). The Health*e*Steps™ program is grounded in scientific evidence [41–46] and members of our pan-Canadian Health*e*Steps™ Network have demonstrated that the program can be applied to numerous community-based settings in urban and rural areas.

## Methods

### Study aims

Adapt FFIT to hockey within the Canadian context, and then integrate this with Health*e*Steps™ to develop Hockey FIT for delivery in Ontario Junior A Hockey Team sites (within the OHL);Explore the potential for Hockey FIT to help overweight or obese men lose weight, increase their physical activity levels, and make improvements in other lifestyle and health-related outcomes by 12 weeks, and then retain these improvements to 12 months;Evaluate feasibility of: a) recruiting men who are overweight or obese into a program focused on physical activity, exercise and healthy eating delivered in collaboration with OHL teams by trained Hockey FIT coaches); and b) retaining these men in both the program and for measurement sessions;Evaluate the acceptability of the Hockey FIT program and research procedures;Conduct Hockey FIT program optimization via a process evaluation.

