### Aim 2: Potential for Hockey FIT to positively impact health outcomes

#### Study design

We conducted a 12-week, two-arm, pilot pRCT of Hockey FIT, as well as a process evaluation of the Hockey FIT program, in which male hockey fans of two OHL teams (London Knights and Sarnia Sting), were individually randomized (1:1) to the Intervention (Hockey FIT) group (starting Hockey FIT program immediately) or the Comparator (Wait-List Control) group (starting Hockey FIT program after a 12-week delay). The 12-week active phase of the Hockey FIT intervention was followed by a 40-week maintenance phase. Measurement sessions were conducted at baseline and 12 weeks (both groups) and then again at 12 months (intervention group only). See Fig. 1 for study flow diagram.

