#### Sample size

A recruitment target of 80 male hockey fans of the London Knights and Sarnia Sting (40 per team; 20 men per arm within each team) was based on a sample size calculation for a subsequent full-scale RCT, following methods by FFIT [15]. To detect a 5 % difference in weight loss between intervention and comparison groups at 12 months, with a standard deviation of 19.9 %, 80 % power and a 0.05 two-sided significance level, 250 men are required in each arm [50]. To allow for 25 % loss to follow-up, a very conservative estimate, the sample size was increased to 335 men in each arm. A target of 670 men reflects the need to recruit 40 male hockey fans from 17 different OHL teams. The need to recruit 40 male hockey fans per site is reflected in this pilot trial.

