##### Participant self-reports at screening and information from baseline measurement sessions

Potential participants were contacted by the research coordinator and screened via email or phone to assess initial eligibility including: gender, age, height, weight, and how they heard about the Hockey FIT program. If the potential participant was deemed “likely” to be eligible after this stage, they were invited to a formal in-person screening session. Once registered in the program, participants attended a baseline measurement session, and demographic information was gathered such as age, postal code, marital status, education, occupation, and ethnicity, overall self-rated health, and clinical characteristics (described in greater detail in the outcome measures section above). These measures were collected to compare the demographics and health of the Hockey FIT participants to the health of men in the general Canadian population.

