##### 12-week non-completer telephone interviews

Non-completers were defined as participants randomized to the intervention group who attended less than six program sessions (<50 %) and did not attend any of the final six program sessions.

Non-completers were contacted after all 12 sessions were completed and were asked to complete a program exit survey over the phone. Participants were asked about why they initially joined the program, why they stopped attending the program, if their involvement in the program has changed their lifestyle habits, and if (and how) the program could be changed to encourage them to complete the program.

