##### 12-week participant program questionnaire

Participants randomized to the intervention group who had attended a minimum of six Hockey FIT coaching sessions (50 %), including at least one of the sessions in the final six weeks of the intervention were asked to complete a 12-week online questionnaire. The program questionnaires, created through the Qualtrics® platform, were e-mailed to participants via an individual link immediately following the final program session. A reminder was sent to men who had not completed the questionnaire after the final session. Questions explored reasons for joining, usefulness of program components, experience with the program and coaches, and any suggestions for improvement.

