##### 12-week participant focus groups

At both sites, participants randomized to the intervention group were asked during sessions 11 and 12 to sign-up for a pre-determined focus group time slot. Focus groups were audio-recorded, semi-structured in nature, and moderated by a trained qualitative interviewer at both sites. Questions explored participants’ reasons for joining the program, experience with the program and health behaviour changes, and suggestions for future program improvement. Along with the interviewer, there was also an observer who made notes about group interactions, dynamics and flow of the focus group discussion. Focus groups were an hour and a half in length and the men were provided with healthy snacks, beverages and water bottles as a token of appreciation.

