##### 12-month participant program questionnaire

During the 12-month measurement session, intervention group participants were asked to fill out a questionnaire detailing their overall experience with the program and their experience with maintaining their healthy lifestyle behaviours, including use of eHealth technology support tools, following the active phase of the program. Participants were also asked whether they would recommend the program to others.

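### Aim 4 covers the acceptability of research procedures, but its one direct measure is fixed near 100 % by the order of consent, and wait-list men have no described route to give their views

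*Protocol article*

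**What the plan says.** Under Study aims, the fourth aim is to "Evaluate the acceptability of the Hockey FIT program and research procedures". The heading over Aims 3–5 repeats both halves. The Abstract and the Discussion mention only the acceptability of Hockey FIT itself.

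Men are "individually randomized (1:1) to the Intervention (Hockey FIT) group" or to a wait-list, with a planned size of "40 per team; 20 men per arm within each team".

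The feedback sources after allocation are described as follows:
- Exit interviews: "Non-completers were defined as participants randomized to the intervention group" with low attendance.
- 12-week questionnaire: sent to intervention men with at least six sessions, including one in the last six weeks. "Questions explored reasons for joining, usefulness of program components, experience with the program and coaches, and any suggestions for improvement".
- Focus groups: "participants randomized to the intervention group were asked during sessions 11 and 12 to sign-up for a pre-determined focus group time slot".
- 12-month questionnaire: "intervention group participants were asked to fill out a questionnaire detailing their overall experience with the program", and with keeping up lifestyle changes.
- 12-month interviews: all willing intervention men.
- Coaches: interviews at 12 weeks and reflections after each session.

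One source covers men of both later arms, before allocation: "Once registered in the program, participants attended a baseline measurement session, and demographic information was gathered". What it collects is eligibility, recruitment route, demographics and health.

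The section Process evaluation & program optimization adds that acceptability of randomization will be estimated from the share of eligible men at baseline who consented. Aim 3b adds retention for measurement sessions.

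**The concern.** A pilot for a wait-list trial has to learn whether men tolerate being randomized, being made to wait, and completing the visits, the 7-day pedometer log and the questionnaires. Only comparator men can report on waiting. If their views are not sought, and the one direct measure cannot vary, the trial could still conclude that its research procedures were acceptable, resting on feedback from the men who received the programme straight away. The confirmatory trial (335 men per arm under Sample size) would then inherit an untested control condition and measurement load. Both bear on its retention and missing data.

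**Working it through.** **1. Size of the group not asked.** From Sample size: 2 teams × 2 arms × 20 men = 80, which matches the stated target. Wait-list: 2 × 20 = 40, and 40/80 = 50 %.

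**2. Who each process source covers.** The article describes nine sources.
- Before allocation, all men (1 source): screening and baseline self-reports.
- After allocation, intervention men (5): non-completer interviews, 12-week questionnaire, focus groups, 12-month questionnaire, 12-month interview.
- After allocation, programme delivery (3): attendance records, session observation with coach reflections, coach interviews.

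So 1 + 5 + 3 = 9. Of the eight that follow allocation, none is directed at wait-list men. The topics described for them are the programme, the coaches, behaviour change and maintenance.

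**3. What Table 4 covers.** Its six process measures are reach, reasons for staying or leaving, delivery as designed, men's experience of the programme, coaches' experience, and men's experience of maintaining change. Research procedures appear in 0 of 6. The narrative summaries are to be organized mainly by these measures (Qualitative analysis for process evaluation), so the reporting structure has no place for the topic either.

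**4. What the consent percentage can show.** The order of events, section by section:
- Screening: written consent to the study comes first. PAR-Q, height and weight follow. Eligible men are then invited to baseline.
- Randomization, allocation & blinding: allocation takes place at a later session, after baseline and seven days of step counts.
- Process evaluation & program optimization: the percentage is taken among eligible men at baseline.

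If N men attend baseline by this route, all N have already consented, so the percentage is N/N = 100 %, apart from departures from procedure. Because it is settled before allocation, it cannot reflect a man's reaction to being put on the wait-list, or to follow-up measurements he has not yet had.

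**5. What retention can show.** Return at 12 weeks is observable in both arms. However, comparator men are invited into the programme after that visit, and intervention men receive a $20 card for attending at 12 months. Attendance may reflect these benefits as well as tolerance of the procedures.

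**6. What asking would yield (illustration only).** Assume 75 % of wait-list men find a procedure acceptable.
- All 40 answer: 1.96 × √(0.75 × 0.25/40) = 0.134, about ±13 points.
- 25 % are lost, the allowance used for the full trial, leaving 30: 1.96 × √(0.75 × 0.25/30) = 0.155, about ±15 points.

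The 75 % is not in the article. These figures show what a short survey could deliver and do not measure an error in the plan.

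**The case against.** Three stronger readings are tempting, and the article does not support them.
- A reader might infer that every process instrument is limited to intervention men or coaches. The screening and baseline self-reports cover all men, and recruitment methods and reasons for exclusion are tracked for all.
- A reader might infer that there is no acceptability estimate at all. The consent percentage is one, and retention for measurement sessions is indirect evidence from both arms. The EQ-5D-3L, which both arms complete, is also said to be piloted for ease of use, although no described source asks men about it.
- A reader might infer that only satisfied attenders are heard. Non-completers are interviewed about why they stopped, and the 12-month interview has no attendance threshold.

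A further objection has force. The article summarizes each questionnaire and topic guide in a line or two, and the guides themselves are not shown. Items on randomization, the pedometer log or questionnaire length may exist for intervention men, so their absence cannot be established. This does not reach the wait-list arm, because the restriction to intervention men is written into the source descriptions and does not depend on the guides. The later offer of the same programme to comparator men does not extend these instruments to them. The exit interview, the 12-week questionnaire and the focus groups name men randomized to the intervention, and the 12-month sources name the intervention group.

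Finally, it can be said that consent and retention are enough for an exploratory pilot. Retention has some value. The consent percentage, as defined, has almost none.

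**Conclusion.** The point holds in a limited form. The only direct measure stated for the acceptability of research procedures is near 100 % by construction. Retention is indirect. All described feedback after allocation comes from intervention men or coaches, and no Table 4 measure covers the topic. The 40 planned wait-list men (50 %) have no described route to give views on allocation, waiting or measurement load.

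This rests on two assumptions: that the consent described under Screening is the one counted in the percentage (no second consent is described), and that no wait-list feedback instrument exists outside the article. The first half of Aim 4, acceptability of the programme, is not affected, nor is the comparison of weight and other outcomes. The change is worth making because it is cheap and alters what the pilot can conclude.

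**What to change.** **If the 12-week visit is still ahead:** add a few items to the paper questionnaires that both arms already complete then. They should cover allocation by chance, waiting or starting at once, the measurement visits, the pedometer log and questionnaire length. Report the answers by arm, and add a Table 4 row for acceptability of research procedures. Cost: a few minutes per man and one descriptive table, with no extra visit.

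**If that visit has passed,** as a start in May 2015 and the past tense of much of the text suggest: limit the Aim 4 conclusion to the programme. Report attendance at measurement sessions and completion of questionnaires and pedometer logs by arm, labelled as indirect evidence only. Carry the items into the confirmatory trial. Cost: a change of wording and a table from data already held.

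In either case, do not present the consent percentage as evidence that randomization was acceptable. Taking it over men judged likely eligible at pre-screening would let it vary, but it would still come before allocation.
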